### 2.2. Participants

This pilot study will enroll patients diagnosed with early-stage TNBC at the IRCCS Humanitas Research Hospital. They will be given a web link to complete a monthly pain questionnaire. Those with a Numeric Rating Scale (NRS) ≥4 will be invited to join the study within 4 weeks of the onset or worsening of the pain syndrome. 

Specifically, the inclusion criteria for patients in the study will be the following:Age >18 years;A willingness to participate in the proposed study;Female sex;A histologically confirmed diagnosis of TNBC;Stages I–III;Indicated for neoadjuvant or adjuvant treatment with anthracyclines and taxanes +/− immunotherapy (i.e., pembrolizumab);NRS ≥4;The ability to provide informed consent according to the International Conference on Harmonization (ICH)—Good Clinical Practices (GCP) and national/local regulations.

The exclusion criteria will be as follows:
The recent introduction of analgesic therapies for PSs, with the frequent or continuous use of pain therapies (including non-steroidal anti-inflammatory drugs, steroids, opioids) for chronic PSs; patients on any analgesic therapy will be recruited only if the therapy is stable for at least 3 months;Patients eligible for other therapeutic regimens (e.g., cyclophosphamide, methotrexate, 5-fluorouracil);Patients who have received or are receiving endocrine therapies for oncological or non-oncological reasons (as these can cause PSs and would represent a potential confounding factor);Patients with a strong language barrier;The diagnosis of a second primary synchronous or metachronous neoplasm (within 5 years prior to the diagnosis of TNBC);The diagnosis of a chronic PS secondary to orthopedic, neurological, or rheumatological disease.

Patients will be allowed to modify their pain management strategies, including analgesic medications, as needed. These adjustments will be documented, and such patients will continue to be monitored and included in the study’s analysis, with appropriate statistical adjustments made to account for any changes in their analgesic use, assessed by applying an equianalgesic scale.

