### 2.6. Serum Marker Evaluation

At timepoints T0 and T2, peripheral venous blood samples will also be collected to carry out a panel of blood chemistry tests to research biomarkers that may correlate with PSs and/or with the response/non-response to PNE. Specifically, based on the data in the literature, serum levels of CRP, ESR, IL-6, IL-8, TNF-α, and CGRP will be measured. CRP and ESR will be determined according to the standard method currently used at the IRCCS Humanitas Research Hospital clinical analysis laboratory. IL-6, IL-8, TNF-α, and CGRP will be assessed through an enzyme-linked immunosorbent assay (ELISA) following the manufacturer’s instructions, as reported elsewhere [17,39].

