### 2.7. Statistical Analysis

#### 2.7.1. Sample Size

The population of the prospective group will consist of 30 consecutive early-stage TNBC patients recruited from our institution’s oncology department. Given the innovative nature of this study, which focuses exclusively on early-stage TNBC patients and utilizes PNE interventions administered by specialized staff, the sample size was determined based on prior prospective studies employing similar interventions [40].

To ensure the representativeness of our results and account for potential dropouts, we have incorporated a margin for sample attrition. Based on typical dropout rates observed in clinical studies, we anticipate a dropout rate of approximately 20%. Therefore, to achieve our target of 30 evaluable patients, we plan to initially recruit 36 patients (30/0.8), ensuring that the final sample size remains robust even if some participants withdraw from the study. This approach will help guarantee that our findings are statistically significant and reflective of the broader population of early-stage TNBC patients undergoing PNE interventions. 

Based on preliminary analyses regarding the study’s primary objective, we will evaluate whether the number of participants should be increased to 50 to identify any factors associated with a better or poor response to the study intervention.

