#### 2.7.2. Analysis

Detailed clinical and demographic variables will be recorded for each patient. Frequency tables and descriptive statistics (mean, standard deviation, percentage, median, range) will be used to summarize patient characteristics. 

Both the total score and the score for each domain will be calculated for each questionnaire, according to the nature of the questionnaire. The expected overall clinical improvement will be assessed based on the variation in the total scores of the administered assessment questionnaires at different timepoints (T0, T1, and T2). A positive response to PNE is defined as a 50% or greater improvement in patient-reported outcomes.

Changes in the levels of serum biomarkers between T0 and T2 (baseline and end of training) will be separately analyzed among patients who have responded to PNE (defined as an improvement in patient-reported outcomes of at least 50%) compared to non-responders using a generalized linear model in which the factors involved in the analysis will be the groups (responders/non-responders) and the timepoints (intra-group variable).

As variables of interest and covariates, demographic data, education level, comorbidities, risk factors for BC (e.g., body mass index, cigarette smoking), and menopausal status at diagnosis will be recorded. Additional covariates to be considered include anxiety and depression, which are closely linked to the perception of pain and the experience associated with it.

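### The biomarker analysis cuts response at 50% in about 30 patients and names no anticancer-treatment covariate, which loses information and leaves the marker–response link open to confounding by treatment phase

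*Protocol article*

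**What the plan says.** Section 2.7.2 (Analysis) sets the group factor: "A positive response to PNE is defined as a 50% or greater improvement in patient-reported outcomes". Marker changes from T0 to T2 are then examined in responders "compared to non-responders using a generalized linear model in which the factors involved in the analysis will be the groups (responders/non-responders) and the timepoints", and the parenthesis that follows labels timepoint as an intra-group variable. This serves the secondary objective in Section 2.4 on whether markers before and after PNE correlate with response to it.

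The covariates named in the same section are demographics, education, comorbidities, "risk factors for BC (e.g., body mass index, cigarette smoking), and menopausal status at diagnosis will be recorded", with anxiety and depression as further candidates. Neither treatment phase nor time since the last infusion is named.

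On treatment, Section 2.2 requires patients to be "Indicated for neoadjuvant or adjuvant treatment with anthracyclines and taxanes", with or without immunotherapy, and the Discussion describes the cohort as being under treatment. On timing, Section 2.6 says "At timepoints T0 and T2, peripheral venous blood samples will also be collected". T0 follows the onset or worsening of pain (Section 2.2), and T2 is the end of a 10-week programme (Section 2.3). Neither draw is tied to a point in the oncological treatment.

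On size, Section 2.7.1 states: "The population of the prospective group will consist of 30 consecutive early-stage TNBC patients".

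**The concern.** There are two weaknesses.

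**The split.** The objective asks about correlation with response, and the patient-reported outcomes are graded scores. Cutting them at 50% treats a patient with 49% improvement like one with none, and a patient with 51% like one with complete relief. With about 30 patients there is little information to spare.

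**Treatment phase.** Two patients at T0 may be at different points of their treatment, and one patient may change phase between T0 and T2. The Introduction itself attributes pain to taxanes and to surgery, so phase plausibly affects response. If phase also shifts the markers, it is a common cause of both, and there is no comparison arm to reveal it. The protocol takes this kind of risk seriously elsewhere: Section 2.2 excludes endocrine therapy as a potential confounder and promises adjustment for analgesic changes. The treatment for which every participant is indicated gets no such control.

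At stake is the biomarker conclusion: a real association could be missed, or an association with treatment phase could be read as an association with response to PNE.

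**Working it through.** **Inputs from the protocol:** 30 patients (Section 2.7.1); response cut at 50% improvement, draws at T0 and T2, and the covariate list (Section 2.7.2). The article gives no power, effect size or SD for the biomarker analysis, so there is no figure of its own to reproduce. (The one printed size calculation, 36 recruits from 30/0.8, gives 37.5, that is 38. It does not affect this point.)

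**Assumptions, because the documents give none:** responder share 20–50%; true correlation between marker change and outcome change 0.3–0.5; phase shift in marker change 0.5–1.5 SD.

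**Step 1. Information kept by the split.** For a normal score cut so that a share p responds, the efficiency is E = φ(z_p)² / [p(1 − p)].

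- p = 0.50: 0.399² / 0.25 = 0.64
- p = 0.33: E = 0.59
- p = 0.20: 0.280² / 0.16 = 0.49

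Thirty patients then act like about 19 (50% responders) or 15 (20%).

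**Step 2. Power at n = 30, two-sided 5%.** The split reduces the correlation to ρ√E. Power ≈ Φ(√(n − 3) · atanh(r) − 1.96).

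- Continuous, ρ = 0.5: 5.196 × 0.549 − 1.96 = 0.89, power 81%
- Split, 50% responders: r = 0.5 × √0.637 = 0.399, power 59%
- Split, 33% responders: r = 0.384, power 56%
- Split, 20% responders: r = 0.5 × √0.490 = 0.350, power 48%

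Simulation (20,000 runs per setting, responder shares 20–50%) agrees:

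| True correlation | Continuous | Split |
|---|---|---|
| 0.3 | about 37% | 20–25% |
| 0.4 | about 61% | 33–41% |
| 0.5 | about 83% | 49–62% |

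**Step 3. Uneven treatment phase.** Simulated t-test of marker change, 12 responders versus 18 non-responders, with no true marker–response link. Patients in one phase have their change shifted by the stated amount. The expected spurious difference is the shift times the difference in phase shares; at 70/30 and 1 SD it is (0.7 − 0.3) × 1 = 0.4 SD.

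| Share in that phase, responders/non-responders | 0.5 SD | 1 SD | 1.5 SD |
|---|---|---|---|
| 50/50 | 5% | 5% | 5% |
| 60/40 | 6% | 7% | 10% |
| 70/30 | 8% | 16% | 26% |
| 80/20 | 12% | 31% | 52% |

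Entries are false-positive rates at a nominal 5%.

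**Step 4. Cost of adjusting.** With k control variables, replace n − 3 by n − 3 − k. For log T0 plus one phase term (k = 2) at a partial correlation of 0.5: √25 × 0.549 − 1.96 = 0.79, power 78%. With five control terms: √22 × 0.549 − 1.96 = 0.62, power 73%. Both ignore collinearity. A parsimonious adjustment therefore costs little, and a long covariate list costs more.

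**The case against.** **The split follows the protocol's own language.** Section 2.6 speaks of response and non-response, and low power in a secondary analysis of a pilot is not in itself an error. Both are true. But Section 2.4 asks about correlation, and the continuous analysis answers that question with the same data. Section 2.7.1 also says "we will evaluate whether the number of participants should be increased to 50". That would help without removing the loss: 50 × 0.49 = 24.5 and 50 × 0.64 = 32, so 50 split patients inform about as well as 25–32 analysed continuously.

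**The covariate list may not be exhaustive.** Section 2.7.2 records detailed clinical variables, and Section 2.2 adjusts for analgesic changes. This shows that treatment data are probably at hand. It does not make treatment phase a planned adjustment.

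**Stronger readings that the document does not support:**

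- A reader might infer that the model has no patient term, so that its standard errors are wrong. The sentence is about T0–T2 changes and calls timepoint an intra-group variable, which most naturally means a repeated, within-patient factor. The wording is ambiguous, and the full protocol or analysis plan may settle it. Even if the pairing were ignored, the group-by-time test would be conservative (simulated size 0.020 to 0.001 for within-patient correlations of 0.3 to 0.7).
- A reader might infer that treatment cycles will drive the result. That needs both a phase effect on the markers and an uneven phase mix. With balanced phase the error rate stays at 5%.
- A reader might take the cut to be on pain. The section says patient-reported outcomes and names no instrument.
- Multiplicity control over the markers is ordinary content of an analysis plan, and its absence here is no finding.

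**Conclusion.** The point holds as an improvement to a secondary analysis. As written, the 50% split gives up about 36–51% of the information (1 − 0.64 to 1 − 0.49). At a true correlation of 0.5, that takes power from about 81% to 48–59%. These figures assume an approximately normal change score and 20–50% responders.

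The missing treatment covariate is a conditional risk. With a 1 SD phase shift the false-positive rate runs from 5% (balanced) through 7% (60/40) and 16% (70/30) to 31% (80/20). The shift and the imbalance are assumptions. What the article does establish is that patients are on treatment, that draws are timed by pain onset and the PNE programme, and that no anticancer-treatment variable is named. The primary objective is unaffected.

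**What to change.** In Section 2.7.2:

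1. For each marker, regress log T2 on log T0 and the continuous T0–T2 change in the patient-reported outcome that defines response, and name that outcome.
2. Add one parsimonious treatment-phase covariate from the clinical record, for example on chemotherapy or not at T2, or a change of phase between T0 and T2.
3. Record time since the last infusion at both draws.
4. Keep responders versus non-responders as a descriptive summary.

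This model, or an equivalent one with a patient effect, also makes the within-patient structure explicit. The blood-draw schedule need not change.

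The cost is one or two degrees of freedom per model (about 78% power instead of 81% in Step 4, where the baseline marker and one phase term are the controls) and slightly more data abstraction.

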### 2.8. Data Management

All data obtained in the study described in this protocol will be recorded on electronic case report forms (eCRFs). All data requested on the CRF will be recorded, and any missing data will be explained. If a space is left blank because the procedure was not carried out or the question was not asked, “N/D” will be noted. If the item is not applicable to the individual case, “N/A” will be noted. The CRFs will be dated, completed chronologically, and updated regularly in order to reflect the most recent data on the patients included in the study. All the collected and updated laboratory data will be kept together in a folder in the laboratory. All copies of the laboratory and clinical data will be kept and updated with the same modalities in digital format (eCRF). The Principal Investigator is responsible for ensuring that the data entered into eCRFs are complete and accurate and that entries and updates are performed in a timely manner. Data regarding sample identity, treatment, and processing will also be reported in the laboratory journal, which is permanently located in the laboratory. 

In addition, data from questionnaires will be collected in an anonymous form and kept with the same modalities of laboratory and clinical data.

### 2.9. Data Ownership and Dissemination Policy

According to the IRCCS Humanitas Research Hospital Guidelines on Good Clinical Practice, the sponsor of the study (the institution, should the investigator or study coordinator act as a sponsor in the performance of her/his institutional duties under the employment or collaboration agreement with IRCCS Humanitas Research Hospital) is the owner of the data resulting therefrom. All investigators participating in the study should be made aware of this circumstance and instructed not to disseminate information or data without the institution’s prior express consent. 

Nevertheless, according to the IRCCS Humanitas Research Hospital Guidelines, to grant public access to the full dataset, the database derived from the study will be uploaded to the Zenodo repository (https://zenodo.org/). 

After the completion of the study, the project coordinator will prepare a draft manuscript containing the final results of the study on the basis of the statistical analysis. The manuscript will be distributed to the co-authors for comments and, after revision, will be sent to a major scientific journal. All publications, abstracts, presentations, manuscripts, and slides, including data from the present study, will be submitted to and reviewed by the study coordinator for coordination and homogeneity purposes. In addition, data will be shared with the patients’ foundation “Sorrisi in Rosa by Pink Union” in order to promote a sensitization and awareness campaign on BC-related pain management.

## 3. Discussion

In this study, we plan to examine the activity of a program that combines PNE and cognitive training. We anticipate that it will enhance coping strategies, reduce disability, and improve patients’ QoL.

Thus, the present study will improve the knowledge on the feasibility of administering a PNE protocol to BC patients and, specifically, to early TNBC patients, providing data on the efficacy of PNE in reducing pain and improving patients’ QoL. To our knowledge, this study is the first to test a PNE intervention in early TNBC patients under treatment. To date, only a few clinical trials have investigated the potential efficacy of PNE in reducing chronic postoperative pain in BC patients, with conflicting results [40,41,42,43]. Among the completed trials, only the study by Manfuku and colleagues demonstrated a statistically significant effect of PNE in decreasing pain [43]. Possible biases in the selection criteria could explain the lack of reliability among study findings, for example, the inclusion of patients experiencing low pain intensity. To overcome this issue, we will include only BC patients who experience at least a moderate level of pain (i.e., NRS ≥4). This issue was also addressed in the PaiNEd trial, in which the research group added an inclusion criterion of a visual analog scale ≥ 4 in regions related to the tumor area [41]. 

The existing data suggest that the most effective PNE program for BC patients should be administered by an experienced professional and last longer than current models. However, there is still a knowledge gap in optimizing this therapeutic approach. Undergoing cancer-related therapies is often overwhelming for BC patients. As a result, they often neglect the “side” aspects of their disease due to their busy schedules and main focus on the cancer diagnosis and cure, even in the early setting [8]. Addressing these issues by exploring additional management strategies is crucial. In this context, the implementation of a PNE program for early TNBC patients could be very interesting, as these women are often young and active patients who might be more receptive to educational interventions aimed at promoting their overall well-being and active role in society.

The project outcomes will directly benefit the target population by providing innovative pain management strategies through an exploratory, personalized PNE program delivered by a physiotherapist with experience in PNE programs across different chronic pain populations. The project will also provide medical oncologists with a standardized approach to improving QoL, pain management, and, eventually, patient outcomes. If the project’s outcomes are reached, they will be validated in a larger multi-centric randomized trial, leading to the potential widespread implementation of the PNE program as a standard pain management tool to be integrated into the therapeutic approach for early TNBC patients.

Finally, due to its flexibility, PNE could be extended to other subtypes of BC and to chronic conditions associated with a high incidence of complications and sequelae.

## Data Availability

No new data were created or analyzed in this study. Data sharing is not applicable to this article.
